
### Data collection methods

#### The first stage

At this stage, data is collected separately through in-depth semi-structured interviews with adolescents, parents, and health professionals. Informed consent will be obtained before the interview. Interviews will be conducted by the researcher, using the interview guide questions. To minimize the differences between the interviewer and the respondents, the interviewer will make use of ice-breaking questions, appropriate language, active listening, and calm body language. All interviews will be transcribed verbatim. They will be analyzed and the codes will be extracted.

#### The second stage

At this stage, to determine construct validity, based on the list prepared by the Department of Education, six girls’ schools and six boys’ schools were randomly selected. From each school and each grade—within the 10–19-year-old age group—a class will be selected in a cluster random sample. The number of samples per item will be 5–10 samples. At this stage, we collect data using a questionnaire prepared in the previous stage, which has both face and content validity.

#### The third stage

At this stage, we use a researcher-made questionnaire the validity and reliability of which were determined in the second stage. The desired questionnaire is uploaded on the application and after installation, this program will be available to people for 3 months. After 3 months of the intervention, by an SMS or a phone call, the people of both groups are asked to complete the questionnaire uploaded, which is in the form of a post-test, and send it back to the researcher. After collecting the data, analysis is conducted by statistical tests.

### Methods of analysis

In the first stage, after the interviews are completed, all the interviews will be transcribed verbatim and entered into NVIVO 12 (Qualitative Analysis Software) for data management. Demographic data will be encoded and analyzed using Microsoft Excel software to determine central indicators and values in a sampling distribution. The data will be analyzed to provide a simple descriptive summary of participants’ opinions presented in everyday language. Specifically, the data will be coded for all the participants and classified to reflect the main themes. In the second stage, we employ factor analysis which is a statistical method that determines the number and nature of variables that a test measures. Following this method, variables with homogeneous correlations are categorized in the form of new variables called factors. The purpose of exploratory factor analysis is to discover the dimensions and common applications including instrument dimensions, standardization of questionnaires or tests, dimensionality, and evaluation of consistency and differentiation in the discussion of construct validity [23]. In the third stage, descriptive statistics (frequency, frequency percentage, mean, and standard deviation) will be used to analyze the data. The Kolmogorov–Smirnov test will also be used to check the normality of quantitative variables. Between-group and within-group comparisons about quantitative variables, independent *t*-test and paired *t*-test, and analysis of variance will be calculated. The chi-square test and Fisher’s exact test in SPSS 16 software will be utilized to test the homogeneity of qualitative variables between the two groups.

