#### The third stage

The next stage of the sampling method is cluster random. From 337 government schools and 93 non-government schools, based on the list of urban schools received from the Department of Education, two boys’ schools and two girls’ schools are randomly selected. Then, one boy’s school and one girl’s school will be randomly assigned as the intervention group and one boy’s school and one girl’s school will be in the control group, and the sampling of students of different grades of the selected schools will be simple cluster or random. Sampling of students from different grades from selected schools will be simple in cluster or random. The sample size was calculated according to the formula of 43 people in each group. Taking into account 15% attrition, the sample size was determined to be 50 people in each group. The study will be conducted on 100 students of Amol City. Of these, 50 people will be assigned to the intervention group and 50 people will be assigned to the control group. From each school, 25 samples were selected (Fig. 2).

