#### Stage III

The third stage is an interventional method of experimental study. This research will be conducted through a pre-test-post-test design with a control group. All the students studying in schools constitute the research community. The researcher first introduces the adolescents to the full explanation of the research and its goals. Then informed written consent will be obtained from the volunteers. None of the participants will be subject to any other research intervention. Schools will be randomly assigned to one of the two intervention (group 1) and control (group 2) groups. The full content of the program will be visible only to the participants in the intervention group. Participants in the control group will be able to download the app after the end of the intervention to use the educational benefits of the app. A self-care application can be used online and offline designed for smartphones running the Android operating system. To run this test, eligible students are asked to install the self-care app on their smartphone and see the necessary instructions on how to work with the program in the form of a short guide on the main page of the application. Initially, the participants are asked to complete the self-care questionnaire in the form of a pre-test. Then, the educational content designed for the application is provided for individuals based on national and international guidelines and protocols of (WHO, CDC, FDA, ADF, Ministry of Health and Medicine, Health Education and Health Promotion Office). This program will be available to people for 3 months and after installing the application on their smartphone and entering the information requested from the users, educational content and reminder messages will be sent according to their conditions. In the reminders section, the user registers his health behavior based on the day, time, and number of times he wants, and a reminder is sent to him. But if the user’s self-care status after answering the self-care questions in each of the 5 dimensions of self-care is assessed as weak or average, motivational health messages are sent to the user daily in the form of notifications, so that the user is encouraged to perform self-care behaviors. The use of the application by the participants is reviewed in the management panel and health messages and incentives are provided for the use of this program. To provide support, the researcher’s phone number is given to the subjects to make a call in case of problems. Three months after the intervention, when no new content is sent to the student, the participants in both groups are requested to complete the self-care questionnaire in the form of a post-test. After the end of the data collection process, the individuals in the control group can install a mobile Application and the necessary training will be given to them after the end of the study. In the present study, content, information, and experiences reach the end users or audience with the specific purpose of self-care through mobile applications in the form of text, audio, or other art forms. Users find and use health-related self-care information through content. The graphic design of the application is based on the opinion of the research team professional designers and application development experts. The production of the content is based on the points extracted from the interviews, national and international guidelines, and protocols of (WHO, CDC, FDA, Ministry of Health and Medicine, Health Education and Health Promotion Office), for example, Australian dietary guidelines, Canberra: NHMRC [20], WHO guidelines on physical activity and sedentary behavior for children and adolescents aged 5–17 years: summary of the evidence [21], and physical activity guidelines [22].

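### Stage 3 randomises four schools, but the arms are compared with pupil-level t-tests/ANOVA, so p-values and intervals are too optimistic by an amount that depends on an unstated ICC

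*Protocol article*

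**What the plan says.** The randomised unit is the school. Under Sampling method (The third stage), the article states that "The next stage of the sampling method is cluster random" and that "two boys’ schools and two girls’ schools are randomly selected". Within each sex, one school goes to each arm: "one boy’s school and one girl’s school will be randomly assigned as the intervention group". Stage III repeats it: "Schools will be randomly assigned to one of the two intervention (group 1) and control (group 2) groups". The cluster size is also given: "From each school, 25 samples were selected (Fig. 2".

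The sample size is individual-level: "The sample size was calculated according to the formula of 43 people in each group", then "Taking into account 15% attrition, the sample size was determined to be 50 people in each group". The formula printed after Fig. 2 is the ordinary two-means formula with no design effect.

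For the third-stage analysis, the Methods of analysis section says: "Between-group and within-group comparisons about quantitative variables, independent *t*-test and paired *t*-test, and analysis of variance will be calculated". The Abstract lists the same tests. The only mention of clusters in connection with the analysis is the sentence after Fig. 2, which adds a covariance adjustment for confounders such as economic status and social class.

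**The concern.** An independent t-test or one-way ANOVA on pupils assumes that the pupils in an arm are independent observations. Pupils in one school share teachers, neighbourhood and peers, so their scores are likely to be correlated. Because whole schools are allocated, that shared component enters the arm difference and averages over only two schools per arm. The pupil-level standard error omits it.

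Effectiveness of the app is the third general goal, and the Discussion says that stage 3 will determine it. If the analysis is run as written, two schools that happen to score better can produce a significant app effect, and the interval will be too narrow.

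**Working it through.** **Inputs from the article.** Two schools per arm, m = 25 pupils per school, 50 pupils per arm, 43 per group before 15% attrition.

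**Assumptions.** Two-sided alpha 0.05 and power 80–90% (the formula is printed without values), and ICC 0.01–0.10 (none is given).

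**The plan's own figure.** The printed formula is n = 2(z₁₋α/₂ + z₁₋β)² / (Δ/S)². Setting n = 43 gives Δ/S = 0.604 at 80% power and 0.699 at 90%. So 43 fits individual randomisation with an effect of about 0.6–0.7 SD and a design effect of 1. The step to 50 is consistent up to rounding: 43/0.85 = 50.6, or 43 × 1.15 = 49.45.

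**Type I error of the planned test.** Design effect DE = 1 + (m − 1) × ICC. The true standard error is √DE times the one the t-test uses, so the true error is about 2[1 − Φ(1.96/√DE)]. For ICC 0.05, DE = 1 + 24 × 0.05 = 2.20, √DE = 1.48, and 2[1 − Φ(1.32)] ≈ 0.19. The simulation used 40,000 no-effect trials of four schools of 25 with total SD 1.

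| Assumed ICC | DE | SE too small by factor | Effective n per arm (50/DE) | Type I error, formula | Type I error, simulated | Coverage of the 95% interval |
|---|---|---|---|---|---|---|
| 0.01 | 1.24 | 1.11 | 40 | 7.8% | about 8% | about 92% |
| 0.02 | 1.48 | 1.22 | 34 | 10.7% | about 11% | about 89% |
| 0.05 | 2.20 | 1.48 | 23 | 18.6% | about 19% | about 81% |
| 0.10 | 3.40 | 1.84 | 15 | 28.8% | about 30% | about 70% |

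With 21 pupils per school after attrition (0.85 × 25 = 21.25), the simulated errors are about 7%, 10%, 17% and 27%. With an assumed 0.5 SD difference between boys and girls, which the pairing by sex balances across arms, they are 7.0%, 17.6% and 28.2% at ICC 0.01, 0.05 and 0.10.

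**What four schools allow.**
- Fitting arm and sex to four school means leaves 4 − 3 = 1 df (critical t 12.7). Ignoring sex leaves 4 − 2 = 2 df (critical t 4.30). The pupil-level test uses 98 df (critical t 1.98).
- The 2-df test holds about 5% if the sexes do not differ. With a 0.5 SD sex difference it rejects in only 0.5% (ICC 0.01), 1.4% (0.05) and 2.1% (0.10) of null trials, so it is conservative.
- Allocation within sex gives 2 × 2 = 4 possible assignments. Each has a mirror image with the same absolute difference, so the smallest two-sided randomisation p is 2/4 = 0.5.

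**Would a mixed model rescue it?** Take arm and sex as fixed effects and school as random, with 1 df when the estimated school variance is positive and pooling to pupil level when it is zero. In simulation without a pre-test covariate, the estimate is zero in 62%, 49% and 39% of null trials at ICC 0.01, 0.05 and 0.10. The resulting error is 5.0% at ICC 0.01, 6.4% at 0.02, 9.5% at 0.05 and 12.1% at 0.10.

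**Power of the school-level test** at 0.604–0.699 SD, from the non-central t distribution:
- 1 df: 17–20% at ICC 0.01 and 10–12% at ICC 0.10.
- 2 df: 34–41% at ICC 0.01 and 17–20% at ICC 0.10.

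**The case against.** Three points can be made for the plan.

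First, an article condenses, and analysis of variance is named without its factors; the full plan may include school. This is weak. The independent t-test is named outright for the between-group comparison, and it cannot carry a school term. The criticism concerns a stated test that does not fit the stated design, not a missing detail.

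Second, the covariance adjustment, and use of the pre-test, could absorb part of the between-school variation. That stands in part: adjustment may lower the residual ICC and so move the trial up the table. It does not model the correlation that remains, and it does not tie the degrees of freedom to four schools.

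Third, the ICC is assumed. This stands. A reader might infer that the p-values are grossly wrong whatever the data. The article does not support that: at ICC 0.01 the error is about 8% against 5%, and it becomes large only from about 0.05.

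A reader might also infer that a mixed model with a school effect repairs the analysis by a change of wording, or that it is interchangeable with a comparison of school means. Neither holds with four schools. The model often sets the school variance to zero and reverts to nearly the pupil-level test, and the 1-df and 2-df analyses behave differently when the sexes differ.

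**Conclusion.** The defect is real and must be corrected. The article randomises four schools and tests pupils as if they had been randomised individually, so the planned p-values and intervals for the app effect are not valid when pupils within a school are correlated. The inflation of the 5% error is to about 8%, 11%, 19% and 30% for assumed ICCs of 0.01, 0.02, 0.05 and 0.10, and somewhat less after attrition, with pre-test adjustment or with a sex difference. The design facts come from the article; the ICC range is an assumption. The power figures also assume alpha 0.05 and 80–90% power behind the 43 per group. A correct analysis restores validity but cannot make four schools a confirmatory trial.

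**What to change.** 1. In Methods of analysis, and in the matching sentence of the Abstract, remove the pupil-level independent t-test/ANOVA as the basis for inference on the app effect. Pupil-level summaries can stay as description.
2. Make the between-group analysis a school-level one: pre-test-adjusted school means, compared within the boys' and the girls' pair. Adjust for the pre-test on pupil data or use change scores; as a school-level covariate it would use up the one remaining df.
3. State the degrees of freedom: 1 with sex as stratum, 2 without, noting that the 2-df version is conservative if the sexes differ. Choose one before the outcome data are seen.
4. Do not rely on a mixed model alone, for the reason shown in the working.
5. Report the between-school variation (the four school means and an ICC estimate).
6. State in Methods of analysis and in the Discussion that with two schools per arm stage 3 is preliminary, and that effectiveness will not be claimed from a pupil-level p-value.

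The edit itself is wording and needs no new data. The price, which should be stated openly, is very wide intervals and power of roughly 10–20% (1 df) or 17–41% (2 df) at 0.6–0.7 SD. A confirmatory claim would need more schools per arm. That is a design change, and with recruitment recorded as starting in July 2022 it may no longer be cheap.

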**Fig. 2 Fig2:**
[figure not shown]
The study sampling stages

$$n= \frac{{2\left(Z1-\frac{\alpha }{2}+ Z1-\beta \right)}^{2}}{{\left(\frac{\Delta }{S}\right)}^{2}}$$

The schools selected for the intervention and control groups will be far apart in order to prevent contamination bias. The effects of confounding variables such as economic status and social class will be controlled in the clusters in the data analysis with the covariance test. All samples, education office, school managers, and user panel managers will be blinded.

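### No stated between-group comparison in stage 3 is adjusted for the pre-test self-care score, although that score is collected and the article plans covariance adjustment for other variables

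*Protocol article*

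**What the plan says.** The Stage III section describes the design: "This research will be conducted through a pre-test-post-test design with a control group". At the start, "the participants are asked to complete the self-care questionnaire in the form of a pre-test", and both groups complete the same questionnaire again as a post-test after three months.

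For the analysis of this stage, the Methods of analysis section states: "Between-group and within-group comparisons about quantitative variables, independent *t*-test and paired *t*-test, and analysis of variance will be calculated". The Abstract gives the same list. Neither place says whether the independent t-test is on post-test or change scores, whether the analysis of variance is one-way or repeated-measures, or which of the tests carries the conclusion about the app.

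A further method appears only in Sampling method, The third stage, in the text after Fig. 2: "confounding variables such as economic status and social class will be controlled in the clusters in the data analysis with the covariance test". The pre-test score is not named there, and no covariance analysis is listed in Methods of analysis or in the Abstract.

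On the design, the sampling section says "one boy’s school and one girl’s school will be randomly assigned as the intervention group", with the other boys' school and girls' school as controls, and "From each school, 25 samples were selected". On size: "The sample size was calculated according to the formula of 43 people in each group", raised to 50 for 15% attrition.

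**The concern.** The pre-test is the same instrument as the outcome, taken on the same pupil, so it is the natural covariate. The article commits to specific tests in two places, and none of them is stated to adjust the between-arm comparison for it. Two things are at stake.

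First, only two schools per arm are randomised, so the arms may well start at different mean scores. A comparison of post-test means that ignores the start carries part of that difference into the estimated effect and leaves avoidable pupil-level noise in its standard error.

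Second, paired t-tests within each arm are listed alongside the between-arm test with no order of importance. A change within one arm mixes the app with three months of maturation, re-testing and school-year effects. The control arm exists to remove these.

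**Working it through.** **The plan's own figure.** 43 × 1.15 = 49.45, which rounds up to the stated 50 per group (43 / 0.85 = 50.6 would give 51). The printed formula is n = 2(z₁₋α/₂ + z₁₋β)² / (Δ/S)². The article does not print α, power, Δ or S, so 43 can only be solved backwards. With two-sided α 0.05 and 80% power (assumed), Δ/S = √(2/43) × (1.960 + 0.842) = 0.604. With 90% power it is 0.699. The formula is for an unadjusted comparison of two means and has no pre/post correlation term.

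**Chance baseline difference between arms.** Inputs from the article: 2 schools per arm, 25 pupils per school, so 50 pupils per arm. The ICC is assumed. In units of the pupil SD:

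SD = √{2 × [ICC/2 + (1 − ICC)/50]}

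- ICC 0: √0.0400 = 0.20
- ICC 0.01: √0.0496 = 0.22
- ICC 0.05: √0.0880 = 0.30
- ICC 0.10: √0.1360 = 0.37

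If the post-test regresses on the pre-test with correlation ρ and equal SDs, an unadjusted post-test contrast carries about ρ times the baseline difference. At ICC 0.05 the carried part has an SD of 0.09, 0.15 or 0.21 for ρ = 0.3, 0.5 or 0.7, against the back-solved target of about 0.60. This takes the pupil-level slope to hold for school differences too.

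**Precision.** Residual variance relative to S² is 1 for a post-test t-test, 2(1 − ρ) for a change-score t-test and 1 − ρ² for ANCOVA. The correlation is assumed, clustering is ignored, and power is at 43 per arm with Δ/S = 0.604 and two-sided α 0.05.

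| ρ | Variance removed by ANCOVA | Power, post-test t-test | Power, change-score t-test | Power, ANCOVA | n per arm for 80% with ANCOVA |
|---|---|---|---|---|---|
| 0.3 | 9% | 80% | 65.8% | 83.6% | 40 |
| 0.5 | 25% | 80% | 80.0% | 89.9% | 33 |
| 0.7 | 49% | 80% | 95.1% | 97.5% | 22 |

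The ordering does not depend on the chosen values. 1 − ρ² = (1 − ρ)(1 + ρ) is never above 2(1 − ρ), because 1 + ρ is at most 2, and it is never above 1.

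**Within-arm tests.** Suppose both arms truly change by the same amount, each paired test has power p, and the arms are independent. Exactly one arm is then significant with probability 2p(1 − p): 0.50 at p = 0.5 and 0.32 at p = 0.8. A significant result in one arm only is therefore common when the app adds nothing.

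**Degrees of freedom.** Four schools with an intercept and arm leave 4 − 2 = 2 residual degrees of freedom at school level. Adding sex, which is constant within each school, leaves 1. Adding a school-mean pre-test as well leaves 0.

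**The case against.** A reader might infer that the pre-test plays no part in the between-group comparison. The article does not say that. The independent t-test could be on change scores. With two arms a one-way analysis of variance would only repeat the t-test, so a group-by-time analysis is a plausible reading. Either would use the pre-test. This stands, and it limits the point to what is stated. It does not remove the gain, since ANCOVA is at least as precise as the change-score test.

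A reader might also infer that baseline differences pass whole into the effect estimate. They do not. An unadjusted post-test contrast carries only a part, and the sampling section plans some covariance adjustment with an open list of confounders, so the pre-test is unnamed but not excluded.

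Nor does any section say that effectiveness will be judged by significance in one arm and not the other. Between-group comparison is listed first. The 50% and 32% figures show why paired tests cannot serve as evidence of the effect, not what the investigators have announced.

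It is fair to add that an article leaves detail to a full protocol or analysis plan. But this article does name its tests, and its sampling and analysis sections differ on whether a covariance analysis is among them.

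Finally, the sizes are soft. ICC and correlation are assumed, and the power figures treat pupils as independent. The baseline SD is 0.20 even at ICC 0, so the small number of schools explains only part of it. Because each arm has one boys' and one girls' school, the ICC must be read net of sex.

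**Conclusion.** The point holds in limited form. The pre-test is collected, no stated between-group comparison is adjusted for it, and the one planned covariance adjustment names other variables and is missing from the analysis section. Adjusting for the pre-test is a better method than the listed t-tests, at no cost in data.

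The direction of the gain is certain under the usual ANCOVA assumptions. Its size is not, because the article gives neither a pre/post correlation nor an ICC. Over the assumed ranges, ANCOVA removes 9% to 49% of pupil-level residual variance, and the chance baseline difference that it would partly correct has an SD of 0.22 to 0.37 pupil SDs. How much of the between-school variation the pre-test explains is unknown, so the pupil-level gain should not be read as the gain for the trial.

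Baseline adjustment does not cure having two schools per arm. The design effect 1 + 24 × ICC is 1.24, 2.2 or 3.4 at ICC 0.01, 0.05 or 0.10. That is a separate issue.

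**What to change.** In Methods of analysis, and to match in the Abstract, name one primary between-arm contrast: the post-test self-care score by arm, adjusted for the same pupil's pre-test score. State there whether economic status and social class are further covariates, so that this section and the text after Fig. 2 describe one model. Report within-arm changes descriptively and do not present paired t-tests as evidence that the app works.

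Sex need not be added as a school-level covariate. It is balanced between arms by design, and with four schools it would leave 1 residual degree of freedom.

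The cost is wording in three places. The design already collects the pre-test, and neither sample size nor conduct changes. The change should be fixed before the outcome data are analysed.

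### Schools are allocated within sex, but no planned between-group comparison names sex; the stratum should enter the model together with an analysis that accounts for school

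*Protocol article*

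**What the plan says.** Under Sampling method, third stage, the protocol article states that "two boys’ schools and two girls’ schools are randomly selected" and that "one boy’s school and one girl’s school will be randomly assigned as the intervention group", with the other pair as control. It adds that "From each school, 25 samples were selected". Each arm therefore starts with 25 boys and 25 girls, and the allocation is restricted by sex of school.

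Under Methods of analysis, the third-stage sentence beginning "Between-group and within-group comparisons about quantitative variables, independent" goes on to list the independent t-test, the paired t-test and analysis of variance. It names no factors; the Abstract gives the same list. The only adjustment is stated after Fig. 2 in the sampling section: "effects of confounding variables such as economic status and social class will be controlled in the clusters in the data analysis with the covariance test". Sex is not mentioned in any of these places.

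**The concern.** A factor used to restrict allocation normally belongs in the analysis. The design balances sex between the arms, but a two-sample t-test of arm leaves the boy-girl difference in the error term and so makes no use of the balance. The balance is also only guaranteed at enrolment. If losses fall on boys in one arm and girls in the other, an unadjusted difference mixes some of the sex effect with the app effect.

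Each sex also has exactly one intervention and one control school. A pooled comparison cannot show whether an apparent benefit rests on one pair of schools.

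**Working it through.** **Inputs from the protocol article (Sampling method, third stage).** Four schools, two per arm, one of each sex per arm; 25 pupils per school; 43 per group before attrition; 15% attrition; 50 per group. No sex difference and no intraclass correlation (ICC) is given, so both are assumed and shown as ranges. Let d be the boy-girl difference, in within-sex SD units, in whatever score enters the comparison.

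**The plan's own figure.** The starting figure is given as "The sample size was calculated according to the formula of 43 people in each group". The allowance for losses is then stated as "Taking into account 15% attrition, the sample size was determined to be 50 people in each group". 43 × 1.15 = 49.45, rounded up to 50, so the 50 is reproduced (43 / 0.85 would give 51). The 43 itself cannot be checked strictly, because alpha, power and Δ/S have no stated values.

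**Step 1: standard error, clustering set aside.** With equal numbers of boys and girls in each arm, leaving out sex multiplies the standard error by √(1 + d²/4):

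- d = 0.3: √1.0225 = 1.011
- d = 0.5: √1.0625 = 1.031
- d = 0.8: √1.16 = 1.077

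With independent pupils, the type I error of a nominal 5% test falls to about 4.75%, 4.3% and 3.5%. In simulation (20,000 trials of four schools of 25), adding sex brings it back to about 5%.

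**Step 2: dropout.** Bias = d × (proportion of boys in one arm − proportion of boys in the other). Take 43 completers of 50 per arm, so 7 losses.

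- Worst case: all losses are boys in one arm (18 boys, 25 girls remain) and girls in the other (25 boys, 18 girls remain). The proportions differ by 7/43 = 0.163. The bias is 0.049, 0.081 or 0.130 SD for d = 0.3, 0.5 or 0.8.
- Milder case: 20 boys and 23 girls against 23 boys and 20 girls. The proportions differ by 3/43 = 0.070. The bias is 0.021, 0.035 or 0.056 SD.
- Same pattern in both arms (18 boys and 25 girls in each): the proportions are equal and the bias is 0.

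**Step 3: school clustering put back.** Design effect = 1 + (25 − 1) × ICC. The type I errors come from the same simulation with d = 0.5.

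| Assumed ICC | Design effect | SE understated by factor | Type I error, plain t-test | Type I error, sex added, school ignored |
|---|---|---|---|---|
| 0.02 | 1.48 | 1.22 | 9.6% | 10.7% |
| 0.05 | 2.20 | 1.48 | 17.3% | 18.8% |
| 0.10 | 3.40 | 1.84 | 27.7% | 29.7% |

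Adding sex removes variance from a standard error that is already too small, so a pupil-level test that ignores school rejects slightly more often.

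**Step 4: the stratum when school means are analysed.** At ICC 0.05 a school mean has variance 0.05 + 0.95/25 = 0.088. Leaving out a sex difference of 0.5 SD adds d²/2 = 0.125 to the expected within-arm variance of the two school means. The expected standard error is then inflated by √(0.213/0.088) = 1.56. Omitting the stratum thus matters more here. Including it, however, cuts the residual degrees of freedom from 2 to 1 and raises the two-sided 5% critical value from 4.30 to 12.7.

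**The case against.** The strongest reply is that the documents do not exclude sex. The adjustment covers "confounding variables such as economic status and social class will be controlled in the clusters", the words introducing the examples leave the list open, and the analysis of variance has no stated factors. A condensed article may leave the full covariate list to a longer document. This stands to the extent that the supportable statement is that no planned comparison names sex, and a reader who infers that sex is barred from every comparison goes too far. It does not dispose of the point. The article does name its tests and gives examples of its covariates. An independent t-test of arm has no room for a second factor, and the factor passed over is the one on which the allocation is built.

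A second reply is that the effect is small and conservative, and swamped by clustering. That also stands. A reader might infer from Step 1 that the trial's error bars are too wide and its type I error below 5%. That holds only if pupils within a school are independent. At the ICCs shown, the plain t-test rejects too often.

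A third reply concerns dropout. A reader might infer that any imbalance in dropout by sex biases the effect. It does so only if the pattern differs between arms and sex is related to the outcome. Nothing in the documents predicts opposite patterns, so the worst case is an upper bound. Some difference in retention between arms is conceivable, since only the intervention arm receives messages and incentives during the trial, but whether it would also differ by sex is unknown.

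Finally, separate results for the boys' and girls' pairs are additional reporting. Their absence is not an error in itself.

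**Conclusion.** The point holds in a limited form. The allocation is stratified by sex, and no planned between-group comparison names sex. If scores differ by sex by an assumed 0.3 to 0.8 SD, the pupil-level standard error is about 1% to 8% too large from this cause alone, and unadjusted dropout bias is at most about 0.05 to 0.13 SD. Both vanish if scores do not differ by sex. If change or baseline-adjusted scores are compared, d is the sex difference in those, which may be smaller.

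This is not the main fault in the error term. Treating 100 pupils in four randomised schools as independent is a larger error in the opposite direction, and adding sex does not cure it. The sex correction is worth making because it is cheap and follows from the design, but only as part of an analysis that accounts for school.

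**What to change.** In the paragraph after Fig. 2 and in Methods of analysis, state that the planned covariance model includes sex, the allocation stratum, as a fixed factor, and that the between-group comparison accounts for school. Adding sex to the pupil-level model without the second part should not be done. Report the intervention-minus-control difference for the boys' pair and for the girls' pair beside the pooled effect.

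The cost is a sentence or two for the sex term and the paired reporting. Sex is known from the school, so no new data are needed. At pupil level the term uses 1 degree of freedom and leaves about 97 (100 pupils less 3 parameters: intercept, arm and sex). On school means it leaves only 1 residual degree of freedom, so the two within-sex differences should be shown descriptively there and not tested.
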